#### 2.4.2 Secondary outcomes

Secondary outcomes include blood fatigue markers (lactate, ammonia, inorganic phosphorus, LDH, CK, glucose, free fatty acid) (20, 21) measured at baseline and 8 weeks, with samples collected at rest, immediately after treadmill exercise test, and 30 min after recovery; exercise test parameters including anaerobic threshold (AT), maximal oxygen uptake (VO2max), maximal respiratory quotient (RQmax), and maximal heart rate (HRmax) during treadmill exercise test (19); rating of perceived exertion (RPE) assessed using Borg’s 15-point scale (6–20) (22) measured just before the end of each exercise test stage; visual analogue scale (VAS) for subjective fatigue evaluation on a 10 cm horizontal line (0–10); and hand grip strength of the dominant hand measured using a digital dynamometer in a seated position with the elbow flexed at 90 degrees, taking the highest value from three maximum grip efforts alternating between hands with 1-min intervals.

#### 2.4.3 Safety outcomes

Safety will be assessed through monitoring of subjective and objective adverse events, which will be collected through spontaneous reporting by participants, telephone follow-ups, and regular clinical evaluations during scheduled visits. Adverse event documentation will include onset and resolution dates, severity and outcome, actions taken regarding the investigational product, causality assessment, suspected concomitant medications, and any treatments administered. Laboratory tests will be conducted, including complete blood count (WBC, RBC, Hemoglobin, Hematocrit, Platelets), liver function tests (ALP, gamma-GT, AST, ALT, total bilirubin, total protein, albumin), kidney function tests (BUN, creatinine), lipid profile (total cholesterol, triglyceride, HDL-C, LDL-C), inflammation marker (hs-CRP), and urinalysis. Additionally, vital signs, physical examination, and electrocardiogram will be performed to ensure participant safety.

#### 2.4.4 Baseline and covariate assessments

Dietary intake and physical activity levels will be assessed at baseline and 8 weeks to evaluate potential confounding effects on study outcomes. Participants will be instructed to maintain their usual dietary habits throughout the study period. Dietary intake will be assessed using 24-h dietary records (23) completed on 1 weekday prior to baseline and 8-weeks visits. Physical activity will be measured using the Global Physical Activity Questionnaire (GPAQ) (24), with results quantified as Metabolic Equivalent Task (MET) values (25). These measurements will be used as covariates in additional analyses to adjust for potential baseline differences and changes during the intervention period.

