Meanwhile, recent research has suggested the potential anti-fatigue effects of *Pinus koraiensis* leaf extract (PKL). According to a single animal study by Lee et al. (9), PKL extract improved exercise endurance in mice during weight-loaded forced swimming and rotarod tests. In terms of biochemical markers, PKL extract significantly reduced blood lactate and LDH levels related to anaerobic metabolism, as well as decreased CK levels, an indicator of muscle damage. Regarding aerobic metabolism, PKL extract significantly increased the levels of antioxidant enzymes SOD and GSH-Px, which typically decrease after exercise, demonstrating a protective effect against oxidative stress. Additionally, PKL extract improved energy metabolism by increasing glycogen levels in both liver and muscle. These results suggest that PKL extract may exert anti-fatigue effects through metabolic regulation, and antioxidant activity. Based on these promising animal findings, whether these effects also occur in humans has not yet been explored.

Therefore, this study was designed to evaluate whether the anti-fatigue effects of PKL extract observed in previous animal experiments also occur in humans. Specifically, we aim to assess the anti-fatigue and exercise performance-enhancing effects of 8-weeks PKL extract consumption compared to placebo intake in healthy adults with high fatigue levels. If the efficacy of PKL extract in humans is confirmed through this study, it could be developed as a new functional food ingredient for fatigue improvement. This clinical trial was designed as a randomized controlled trial comparing the superiority of the PKL extract group over the placebo group, with parallel comparison between the two groups, and an allocation ratio of 1:1.

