### 2.11 Statistical methods

#### 2.11.1 Analysis set

Efficacy data will be primarily analyzed using the Per-Protocol (PP) set, with additional analyses conducted on the Intent-to-Treat (ITT) and Full Analysis (FA) sets. Safety data will be analyzed using the Safety Analysis (SA) set.

The ITT set will include all participants enrolled in this clinical trial. The SA set will comprise subjects who consumed the investigational product at least once after enrollment. The FA set will include all randomized participants with at least one efficacy evaluation after consuming the investigational product. Participants who violated inclusion/exclusion criteria or never consumed the investigational product will be excluded from the FA set. The PP set will consist of participants from the FA set who completed the trial according to the protocol without major violations. Participants who used prohibited concomitant medications or committed other serious protocol violations will be excluded from the PP set. Other serious protocol violations will be determined through a blind data review meeting.

Statistical analyses will be performed using SAS for Windows, with statistical significance set at *p* < 0.05. Missing values will be replaced using the Last Observation Carried Forward (LOCF) method. Baseline characteristics between groups will be compared using Chi-Square test or Fisher’s exact test for categorical variables and Independent *t*-test for continuous variables.

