#### 2.11.2 Statistical methods for analyzing efficacy outcomes

For primary and secondary efficacy endpoints, descriptive statistics will be presented by treatment group, and comparisons will be made both between groups.

For between-group comparisons, changes from baseline (post-8-weeks consumption minus pre-consumption) will be analyzed using independent *t*-test if normality assumptions are met, or Mann-Whitney U test if not. The proportion of participants showing improvement in efficacy variables at 8 weeks compared to baseline may be analyzed using Chi-Square test or Fisher’s exact test.

For repeated measurements of FSS (excluding the primary efficacy endpoint analysis), VAS for subjective fatigue, and grip strength (measured three times), RM-ANOVA or Linear Mixed Model will be used for between-group comparisons if normality assumptions are met or appropriate non-parametric methods if not. In cases of severe violation of normality assumptions, variable transformation methods such as logarithm transformation may be applied before analysis.

Additionally, ANCOVA or ranked ANCOVA may be performed with covariates including lifestyle factors (dietary intake, physical activity, alcohol consumption, smoking, occupation, etc.), baseline values and changes in lifestyle factors, baseline values of efficacy variables that are not homogeneous between groups, and demographic information.

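### The additional adjusted efficacy models include on-treatment changes in diet and activity, so their estimate need not be the total effect of PKL; the imbalance rule for baseline efficacy values gives up precision

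*Protocol article*

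**What the plan says.** Section 2.4.4 of the protocol article: "Dietary intake and physical activity levels will be assessed at baseline and 8 weeks". The stated purpose is to look for confounding of the study outcomes. On use in the analysis: "These measurements will be used as covariates in additional analyses to adjust for potential baseline differences and changes during the intervention period". Lifestyle is restrained only as to diet: "Participants will be instructed to maintain their usual dietary habits throughout the study period". That instruction does not mention physical activity.

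Section 2.11.2 gives the main between-group comparison: "changes from baseline (post-8-weeks consumption minus pre-consumption) will be analyzed using independent" t-test, or the Mann-Whitney U test if normality fails. It then adds that "ANCOVA or ranked ANCOVA may be performed with covariates including lifestyle factors", and the list goes on to "baseline values and changes in lifestyle factors, baseline values of efficacy variables that are not homogeneous between groups, and demographic information".

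Section 2.11.1 provides baseline tests: "Baseline characteristics between groups will be compared using Chi-Square test" or Fisher's exact test for categorical variables, and the t-test for continuous ones, with significance set at p < 0.05.

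The two sections differ in commitment. Section 2.4.4 says the lifestyle measurements will be used as covariates; section 2.11.2 says the ANCOVA may be performed.

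**The concern.** A variable measured after randomisation cannot confound a randomised comparison in the way a baseline variable can by chance. It may lie on the path from product to outcome, follow from the outcome, or share an unmeasured cause with it.

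In this trial that is plausible for activity. The introduction states the aim: "we aim to assess the anti-fatigue and exercise performance-enhancing effects of 8-weeks PKL extract consumption compared to placebo intake". People who feel less tired, or who can exercise longer, may move more. A model that holds the change in activity fixed then compares the arms after removing part of what the product may have done. If activity change and fatigue also share an unmeasured cause, conditioning on the change can create an apparent difference where none exists. The same reasoning applies to both primary outcomes, FSS and the treadmill test.

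The rule for baseline efficacy values is a separate and smaller matter. Whether the outcome's own baseline value is in the model depends on the observed imbalance, not on how well it predicts the outcome, which is the reason to include it.

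The results are meant for the MFDS and a journal. An adjusted result that disagrees with the main one would be hard to interpret if it could differ for either reason.

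**Working it through.** **1. The plan's own figure.** Section 2.6 gives a difference of 4.59, SD 6.8, two-sided 0.05, power 0.80 and 1:1 allocation.

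n per group = 2 × (1.960 + 0.842)² × 6.8² / 4.59² = 34.45, so 35. With 30% dropout, 35 / 0.70 = 50. Both stated figures reproduce. Power at 35 per group is 0.806 by the normal formula and 0.795 by the noncentral t.

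**2. Adjusting for a change that PKL may cause.** Let PKL shift the activity change by *a* SD, let each SD of activity lower FSS by *b* points, and let the total effect be -4.59. A model that holds activity change fixed estimates

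adjusted effect = -4.59 + *a* × *b*.

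The values of *a* and *b* are assumptions; the documents give none. Simulation used 35 per arm, within-arm SD 6.8 and 6,000 runs per row:

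| *a* (SD) | *b* (points per SD) | Formula | Simulated adjusted estimate | Power, adjusted |
|---|---|---|---|---|
| 0 | 2 | -4.59 | -4.58 | 0.82 |
| 0.3 | 2 | -3.99 | -4.00 | 0.71 |
| 0.5 | 2 | -3.59 | -3.59 | 0.59 |
| 0.5 | 3 | -3.09 | -3.09 | 0.52 |
| 0.8 | 3 | -2.19 | -2.21 | 0.28 |

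Without the change score, the estimate in these rows stayed between -4.57 and -4.60, with power 0.79 to 0.80. In the first row PKL does not move activity, and adjustment causes no bias.

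**3. Common cause, no effect of activity on FSS.** Suppose PKL shifts activity by 0.5 SD, activity has no effect on FSS, and an unmeasured factor loads 0.5 on both (again assumptions). The bias is 0.5 × 0.5 × 0.5 × 6.8 = 0.85 points.

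- True effect -4.59: simulated adjusted estimate -3.73.
- True effect 0: simulated adjusted estimate +0.89, rejection rate 8.0% against 5.2% unadjusted.
- True effect 0 with the loading at 0.3: +0.34, and 5.3% against 4.8%.

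**4. Entering the baseline value only when groups differ.** Simulated with a true effect of 0, 35 per arm, 15,000 runs, and the baseline value entered only if its t-test gave p < 0.05. Section 2.11.2 does not say how homogeneity is judged; the test is inferred from section 2.11.1. The variance ratio is ANCOVA against change score, with equal variances at baseline and 8 weeks: (1 - ρ²) / [2(1 - ρ)] = (1 + ρ) / 2.

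| Correlation ρ, baseline with 8 weeks | Mean estimate | Rejection rate | Variance if always adjusted ÷ variance of change score |
|---|---|---|---|
| 0.3 | 0.00 | 4.1% | 0.65 |
| 0.5 | 0.00 | 4.2% | 0.75 |
| 0.7 | 0.00 | 4.8% | 0.85 |

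The estimate stays centred on the truth and the test is slightly conservative. When the imbalance rule is not triggered, the precision gain in the last column is forgone.

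**The case against.** The strongest reply is that these models are additional and, in section 2.11.2, optional. The efficacy comparison is the unadjusted test on change at 8 weeks; its estimate, error rate and planned power do not depend on the ANCOVA. That stands and limits the weight of the point.

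Second, the bias is conditional. It needs PKL, or the outcome it alters, to move the covariate. The instruction to keep usual eating habits makes this less likely for diet, though it says nothing on activity. That also stands.

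Third, only a condensed article is shown, and the final covariates of a supplementary model are commonly left to the SAP. This is fair for the open-ended list, which is not criticised here. It does not cover the inclusion of change scores or the imbalance condition, which the article states as rules.

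Fourth, any power figure is fragile. If 10%, 20% or 30% of 4.59 ran through activity, 4.13, 3.67 or 3.21 would remain. With the SD held at 6.8, power at 35 per group is 0.71, 0.61 or 0.50. If activity is worth 3 points per SD, the residual SD falls to √(6.8² - 3²) = 6.10 and power is 0.79, 0.69 or 0.56, so at 10% the loss against 0.795 disappears. No particular power loss can be claimed.

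Fifth, the article says the trial follows an MFDS guideline that is not at hand. Whether lifestyle-adjusted results are expected is unknown, which is a reason to allow a labelled exploratory version.

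**Conclusion.** The point holds in a limited form. Sections 2.4.4 and 2.11.2 both place on-treatment changes in diet and activity in the adjusted efficacy models. Such a model need not estimate the total effect of PKL. Under the assumed shifts and slopes, the FSS difference moves from -4.59 to between -4.00 and -2.21. With no PKL effect on the covariate, this adjustment adds no bias.

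A reader might infer three stronger things that the documents do not support:

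- **That the adjusted result is certainly not the effect of PKL.** This needs a PKL effect on diet or activity, for which the documents give no figure.
- **That choosing baseline values by imbalance also biases the estimate.** It does not: the mean estimate was 0.00 under the null. Its costs are precision and a rejection rate of 4.1% to 4.8% instead of 5%. The null rate rises to 7.1% to 7.7% only if the smaller of the unadjusted and adjusted p-values is reported, which no section proposes. The condition is also written only for baseline efficacy values, not for lifestyle baselines or demographics.
- **That the trial's main result is compromised.** It is not.

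**What to change.** In sections 2.4.4 and 2.11.2:

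- Delete changes in lifestyle factors from the covariates of the adjusted efficacy models, and report 8-week diet and activity by arm. If a change-adjusted model is wanted, label it exploratory and state that it is not to be read as the total effect of PKL.
- Replace the homogeneity condition with adjustment for the baseline value of the outcome in every adjusted model. Any further covariates should be baseline-only and fixed before unblinding.
- Align the two sections on whether the adjusted analysis will or may be done.

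The cost is wording; all the data are already being collected. The small downside is that the change-adjusted result is no longer available as an efficacy result.

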### 2.5 Participant timeline

The participant timeline is presented in Figure 1.

**FIGURE 1 F1:**
[figure not shown]
Schedule of enrollment, interventions, and assessments.

### 2.6 Sample size

The sample size of this clinical trial is 50 participants per group. Although no preliminary data on PKL extract’s anti-fatigue effects in humans are available, we referenced a study using fermented porcine placental (FPP) extract (26), which has received Korean MFDS approval for fatigue improvement, as PKL extract is pursuing the same regulatory pathway. In that study, the FPP group (*n* = 36) showed a mean change in FSS score of −9.79, while the placebo group (*n* = 31) demonstrated a mean change of −5.20. Based on the reference study data showing a mean difference of 4.59 points in FSS score change between treatment and placebo groups, and assuming a pooled standard deviation of 6.8, we calculated the required sample size. With a significance level of 0.05 and a power of 0.8 for a two-sided test, we estimated that a minimum of 35 participants per group would be required. Considering an anticipated dropout rate of approximately 30% during the clinical trial process, we decided to recruit a total of 100 participants, with 50 participants per group.

### 2.7 Recruitment

Participants will be recruited through IRB-approved recruitment notices posted within and outside the clinical trial institution, website announcements, and newspaper advertisements.

### 2.8 Random allocation and blinding

An independent statistician generated a randomization list using block randomization methods by SAS for Windows, with the block size remaining undisclosed. Access to the randomization list will be strictly limited. PKL extract and placebo are pre-packaged according to the randomization list, and allocation concealment will be maintained by sequentially assigning enrolled participants to randomization numbers. The PKL extract and placebo capsules have identical appearances, ensuring double blinding throughout the study. Blinding will not be broken until all participants complete the trial and the data is locked. Unblinding will only be permitted in emergency situations where knowledge of the intervention is necessary for participant safety, following established procedures. In such cases, the principal investigator must contact the sponsor as promptly as possible and document the date, time, and reason for unblinding.

### 2.9 Data collection methods

The FSS will be administered to assess the level of fatigue experienced by participants during the preceding week. Investigators will ensure that participants fully understand and can properly respond to the questionnaire. The standardized Korean version of the FSS will be used for this study (18). FSS obtained during the screening phase will be used as baseline values.

A treadmill exercise test will be conducted to measure primary outcomes including time and distance to exhaustion, along with secondary outcomes comprising AT, VO2max, RQmax, and HRmax. Additionally, RPE will be assessed at the conclusion of each stage of the treadmill exercise test, immediately before progressing to the next stage.

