### 2.2 Eligibility criteria

#### 2.2.1 Inclusion criteria

This clinical trial will enroll adult men and women aged 19–60 years at the time of screening who have a Fatigue Severity Scale (FSS) score of 27 or higher. All participants must be fully informed about the clinical trial, understand its details, agree to exercise tolerance testing, and voluntarily decide to participate and comply with precautions as documented by written informed consent.

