### 2.4 Outcomes

#### 2.4.1 Primary outcomes

The Fatigue Severity Scale (FSS) scores change from baseline to 8 weeks is designated as the first primary outcome (17, 18). The FSS is a self-administered questionnaire consisting of 9 items that evaluate the subjective level of fatigue-related disability on a scale of 1–7. Scores below 27 indicate “low fatigue,” scores between 27 and 44 indicate “medium fatigue,” and scores of 45 or above indicate “high fatigue.” FSS will be measured at baseline, 4 weeks, and 8 weeks.

The second primary outcome is the change in time and distance to exhaustion during a treadmill exercise test from baseline to 8 weeks. The exercise test utilizes the Modified Bruce protocol, which progressively increases both speed and incline to measure exercise capacity (19). The test begins at stage 1 (2.7 km/h, 0% grade, 3 min) and continues through predefined stages of increasing difficulty (stage 2: 2.7 km/h, 5% grade, 3 min; stage 3: 2.7 km/h, 10% grade, 3 min; stage 4: 4.0 km/h, 12% grade, 3 min; stage 5: 5.4 km/h, 14% grade, 3 min; stage 6: 6.7 km/h, 16% grade, 3 min; stage 7: 8.0 km/h, 18% grade, 3 min). The test is terminated when the participant voluntarily requests to stop. The distance to exhaustion is calculated using the total exercise duration and speed. Treadmill exercise test will be conducted at baseline, and 8 weeks.

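### The FSS score that qualifies a volunteer is also the FSS baseline, so arm-level changes carry regression to the mean and cheap precision is forgone; the randomised comparison stays unbiased

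*Protocol article*

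**What the plan says.** All references are to the protocol article.

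- Section 2.2.1 admits adults "aged 19–60 years at the time of screening who have a Fatigue Severity Scale (FSS) score of 27 or higher".
- Section 2.4.1 sets the endpoint, "The Fatigue Severity Scale (FSS) scores change from baseline to 8 weeks is designated as the first primary outcome", and the schedule, "FSS will be measured at baseline, 4 weeks, and 8 weeks".
- Section 2.9 says which measurement supplies the baseline: "FSS obtained during the screening phase will be used as baseline values". It also gives the recall window: the FSS is used to "assess the level of fatigue experienced by participants during the preceding week".
- Section 2.11.2 tests raw changes: "changes from baseline (post-8-weeks consumption minus pre-consumption) will be analyzed using independent" *t*-test, or Mann-Whitney U if normality fails. ANCOVA is optional, and baseline efficacy values are named as covariates only where the groups are not homogeneous. The same section allows an optional analysis of "The proportion of participants showing improvement in efficacy variables at 8 weeks compared to baseline".

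The text describes no second FSS before dosing and gives no interval from screening to first capsule. The schedule in Figure 1 is not shown.

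**The concern.** One self-reported score covering a single week both decides entry and anchors every FSS change. People selected for a high score tend to score lower next time without any treatment. Part of the fall in each arm, and part of any improvement rate, is then an artefact of selection. This matters for interpretation because section 4.5 says the results go to the Korean regulator in support of a fatigue-improvement ingredient, where arm-level falls and improvement rates may be read at face value.

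The second issue is efficiency. The endpoint rests on one pre-dose score, and baseline adjustment is optional, although a second short questionnaire or a fixed covariate would tighten the comparison at little cost.

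**Working it through.** **The plan's own figure.** Section 2.6 uses a difference of 4.59, SD 6.8, two-sided 0.05 and power 0.80. Then n = 2 × [6.8 × (1.960 + 0.842) / 4.59]² = 34.45, so 35 per group, and 35 / (1 − 0.30) = 50. Both stated numbers reproduce. Two-sample *t*-test power at 35 per group is 0.795.

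**Assumptions.** The article gives no FSS population mean μ, SD s or between-visit correlation. I take μ/s as 33/10 or 38/9, correlation ρ from 0.6 to 0.8, normal scores, and selection only on screening FSS ≥ 27.

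**Formulas.** Let a = (27 − μ)/s, λ = φ(a)/[1 − Φ(a)] and v = 1 + aλ − λ². For 33/10, λ = 0.459 and v = 0.514. For 38/9, λ = 0.213 and v = 0.695. With no treatment effect and all visits equally correlated:

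- mean fall from the screening score = (1 − ρ)sλ
- variance of change from the screening score = s²[(1 − ρ)²v + 1 − ρ²]
- variance of change from one separate repeat score = 2(1 − ρ)s²
- variance of change from the mean of the two = s²[(ρ − (1+q)/2)²v + (1 − ρ²) + (1 − q²)/4 − ρ(1 − q)], where q is the correlation between the two pre-dose scores (here q = ρ)

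Example, 33/10 with ρ = 0.7:

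- The mean fall is 0.3 × 10 × 0.459 = 1.38.
- The screening variance is 100 × (0.09 × 0.514 + 0.51) = 55.6, SD 7.46.
- The single-repeat variance is 60, SD 7.75.
- The two-score variance is 100 × (0.0225 × 0.514 + 0.51 + 0.1275 − 0.21) = 43.9, SD 6.63.

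| μ/s, ρ | Fall, no effect | Improved, no effect | SD: screening | SD: one repeat | SD: mean of two | Variance ratio, mean of two vs screening |
|---|---|---|---|---|---|---|
| 33/10, 0.6 | 1.84 | 58% | 8.50 | 8.94 | 7.62 | 0.80 |
| 33/10, 0.7 | 1.38 | 57% | 7.46 | 7.75 | 6.63 | 0.79 |
| 33/10, 0.8 | 0.92 | 56% | 6.17 | 6.32 | 5.43 | 0.78 |
| 38/9, 0.6 | 0.77 | 54% | 7.80 | 8.05 | 6.90 | 0.78 |
| 38/9, 0.7 | 0.57 | 53% | 6.81 | 6.97 | 5.99 | 0.77 |
| 38/9, 0.8 | 0.38 | 53% | 5.60 | 5.69 | 4.90 | 0.77 |

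From an unselected, equally correlated repeat score the fall is 0 and 50% improve.

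**Between-group test.** In 20,000 simulated null trials (μ 32, s 10, ρ 0.7, 35 per arm), the mean change was −1.53 within arms. The between-group difference was 0.005 (SE 0.013) and the type I error 0.051.

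**If the two pre-dose scores are closer to each other than to week 8.** Take 33/10. With both correlated 0.7 with week 8, the variance reduction from averaging is 14%, 7% and 3% at q = 0.80, 0.90 and 0.95. If the screening score correlates 0.65 with week 8 and the repeat 0.70, the last term of the formula becomes −(0.70 − 0.65q) and ρ = 0.65 elsewhere. The reductions are then 19%, 13% and 10%. Most of this range lies between 5% and 19%, with 3% at its least favourable corner.

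**Power.** A 22% reduction takes SD 6.8 to 6.8 × √0.78 = 6.01 and power at 35 per group from 0.795 to about 0.88. A 5% to 19% reduction gives about 0.81 to 0.87.

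**ANCOVA.** At 33/10 with ρ = 0.7, adjusting for the screening score alone gives residual SD 10 × √(1 − 0.49) = 7.14, against 7.46 for the raw change. Adjusting for the two-score mean with q = 0.7 gives 10 × √(1 − 0.49/0.85) = 6.51.

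**The case against.** The strongest reply is that nothing in the primary inference is wrong. Randomisation spreads regression to the mean equally over the arms, the type I error holds, and section 2.11.2 plans between-group comparisons only. The improvement proportion is optional and would itself be compared between groups. All of this stands.

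A reader might go further and infer one of the following, none of which the document supports.

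- *The selected baseline adds noise to every FSS change.* In all six scenarios the screening score gives a smaller SD of change than a single unselected repeat. It would be noisier only if it tracked week 8 less well, for instance after a long gap before dosing, and no gap is stated.
- *The selection costs the trial power, 0.80 instead of 0.88.* That gain comes from averaging two measurements and would be available in most trials with one baseline score.
- *Sections 2.4.1 and 2.9 contradict each other.* They do not: 2.9 says which measurement fills the baseline slot.
- *Taking baseline before dosing is a fault, or volunteers inflate their scores to gain entry.* The first is true of any baseline, and the second is conjecture.

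It is also fair to object that averaging does not remove the artefact. With equal correlations the two-score mean keeps half of it, 0.19 to 0.92 points in the scenarios above. This is why the remedy needs a separate rule for descriptive results.

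**Conclusion.** The point holds as one of interpretation and forgone precision, not of validity. Because entry and baseline share one score, each arm's mean FSS change would include a fall of about 0.4 to 1.8 points unrelated to treatment, and 53% to 58% would count as improved under no effect. These figures rest on the assumed means, SDs and correlations.

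The plan does not describe the simple measures that would help: a second pre-dose score and a fixed baseline covariate. The variance gain from averaging is about 20% to 23% with equally correlated visits and about 5% to 19% when the pre-dose scores correlate 0.80 to 0.95. Power of about 0.88 is therefore an upper-range figure, and it assumes that the simulated ratio carries over to the plan's SD of 6.8. A modest change is worth making because it is cheap.

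**What to change.** In section 2.9, replace the sentence on baseline values with wording such as: *The screening FSS determines eligibility. The FSS is repeated before the first capsule. The baseline for the primary FSS change is the mean of the two scores.*

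In section 2.11.2, make ANCOVA with this baseline a prespecified analysis of the primary FSS change, not one that depends on whether the groups look homogeneous. Base any improvement proportion and any descriptive within-arm change on the pre-dose score alone. That score is free of regression to the mean only if the visits are equally correlated. If the two pre-dose scores correlate 0.80 and each correlates 0.70 with week 8, it still keeps (0.80 − 0.70)/(1 − 0.70), one third of the fall, while the two-score mean keeps two thirds. It remains the better choice for description.

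The cost is one more 9-item self-completed questionnaire and a few sentences of text. Within-arm falls will look slightly smaller, and FSS will have one reference for the primary test and another for description, which must be labelled. If screening and first dose are close together, the gain is small. Where the repeat cannot be added, the prespecified ANCOVA on the existing screening score needs no new data, but it recovers less precision and leaves the arm-level artefact in place.
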